### Data collection

Early identification of patients, resource utilization, and place of death will be estimated relative to the number of patients who could benefit from PC services (causes of death: ICD codes C00-C97; 100–152, 160–169, N17, N18, N28, 112, 113, K70-K77, J06-J18, J20-J22, J40-J47, J96, G10, G20, G35; G122, G903, G231.F01, F03, G30, R54, B20-B24), using the calculation of the potential population size for PC developed by Rosenwax [8, 9]. The causes of death will be identified by review of the death certificates of patients who died 9 to 21 months after the onset of PC.

The NECPAL and IDC-PAL are integrated in the electronic records of GPs, thereby allowing early identification of patients needing PC and evaluation of case complexity. We will extract data from the electronic records upon completion of the NECPAL to identify the need for PC, estimate case complexity using IDC-PAL, and record all emergency department visits, outpatient office visits, primary care visits, duration of all hospital stays, and ICU admissions.

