**Methods:**

Design: A two-arm cluster randomized clinical trial of 30 Primary Health Care Centers (PHCC) in Mallorca (Spain), in which each center was randomized to an intervention arm or a usual care arm. We expect that the number of patients identified as suitable for PC (including non-oncological PC) is at least 5% greater in the intervention arm.

Sample size: A total of 4640 deceased patients. Outcomes will be assessed by a blinded external review of the electronic records.

Interventions: General practitioners (GPs) and nurse leaders in PC for each PHCC will be appointed. These leaders will help promote PC training of colleagues, improve symptom management and psychological support of patients, and evaluate the complexity of individual cases so that these cases receive assistance from PC home-based teams.

Measurements: Early identification (>90 days before death), evaluation of case complexity, level of case complexity (with referral to a home-based PC team), use and cost of hospital and primary care services, and quality of life during the last month of life (≥2 emergency room visits, ≥2 hospital admissions, ≥14 days of hospitalization).

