## Methods

### Design

The study is a multicenter two-armed cluster randomized clinical trial in the primary health care setting. The intervention will be evaluated by external review of the records of deceased patients at 18 months after study onset (Fig. 1).

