### Outcome measures

#### Primary outcomes

Early identification (90 days before death), by GPs and nurses, of patients who are least 18 years-old and need PC based on electronic records.

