### Sample size

It is necessary to prospectively analyze 4640 clinical records of deceased patients from the defined population (causes of death: ICD codes C00-C97; 100–152, 160–169, N17, N18, N28, 112, 113, K70-K77, J06-J18, J20-J22, J40-J47, J96, G10, G20, G35; G122, G903, G231.F01, F03, G30, R54, B20-B24) to detect an increase of at least 5% in the proportion of patients identified as needing PC at 1 month before death in the intervention arm, assuming that 12% of patients will need PC in the control arm, a median of 263 patients in each health care center (cluster size), and an intra-class correlation coefficient of 0.015 [34].

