## Discussion

Our objective of establishing PC leaders is to improve the PC provided by general and specific services. A more comprehensive and community-oriented approach to PC will provide better results if multiple health care professionals work together at the end of a patient’s life.

The role of primary health care is important for early identification of patients eligible for PC. The major aim of the proposed intervention is to increase the early identification of patients through the appointment of a specially trained PC leader (primary health care doctor or nurse) to each team. Thus, we expect that this intervention will sensitize doctors and nurses in the primary health care team so they can identify patients earlier using NECPAL, assess case complexity using IDC-PAL, and then provide essential care to patients requiring simple PC or more complex PC (home-based PC teams, or PC units in the hospital) when patient needs exceed their abilities, thereby avoiding hospitals admissions when possible.

The intervention efficacy will be measured as the increased early detection of patients needing PC, and by improvements in care and use of resources. To determine the effectiveness of the intervention, we will use secondary data from patients’ clinical records (administrative data), in each cases whose underlying cause of death was consistent with receipt of PC.

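### The death window that selects the analysed patients has no defined time origin and is not aligned with the 18-month record review

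*Protocol article*

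**What the plan says.** Two sections of the protocol article give the timing of the evaluation.

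- Design: the intervention is assessed by an "external review of the records of deceased patients at 18 months after study onset".
- Data collection: causes of death are taken from the certificates of "patients who died 9 to 21 months after the onset of PC".

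The same Data collection paragraph makes these deaths the denominator. Early identification, resource use and place of death "will be estimated relative to the number of patients who could benefit from PC services", and that number is defined by a list of causes of death. The Discussion agrees: records are used "in each cases whose underlying cause of death was consistent with receipt of PC".

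The primary outcome is "Early identification (90 days before death), by GPs and nurses"; the abstract has "Early identification (>90 days before death". The sample size is set "to detect an increase of at least 5% in the proportion of patients identified as needing PC at 1 month before death", "assuming that 12% of patients will need PC in the control arm".

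The inclusion and exclusion criteria are for centres only. At patient level, the cause-of-death list, the age limit of 18 in the primary outcome and the death window together decide who is analysed.

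**The concern.** The outcomes come from routine records of people who have died, so the death window acts as an eligibility criterion and fixes the denominator of the primary outcome. It therefore needs a clear start, a clear end and an origin that means the same in both arms.

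As written, it has none of these with certainty. The review date and the death window are counted from differently named origins, and the text does not relate them. If the origins coincide, the review is dated before the window closes. If the second origin belongs to the individual patient, entry to the analysis depends on an event after randomisation that lies close to the outcome, and patients who were never identified are left out. Either way, someone extracting the data has to make a decision that the protocol should have made.

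**Working it through.** **Inputs.** Review at month 18 (Design). Deaths in months 9 to 21 (Data collection). Early identification at 90 days before death (Primary outcomes). Control rate 12%, increase 5%, intra-class correlation 0.015, 4640 records, median 263 per centre (Sample size). 30 centres (Randomization). Assumptions: the 5% is absolute (12% against 17%), 15 centres per arm, two-sided alpha 0.05, deaths evenly spread over time.

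**Reading A: the origin is the start of the study or intervention.**
- Window length: 21 − 9 = 12 months.
- Part after the review date: 21 − 18 = 3 months.
- Share of the deaths not yet available: 3/12 = 25%.

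**Reading B: the origin is each patient's own start of palliative care.**
- Every included patient started at least 9 months before death: 9 × 30.4 ≈ 274 days, against a threshold of 90 days.
- A patient who never started has no origin and cannot enter.
- Compare the rest of the plan: the denominator is all deaths from listed causes, and the planned proportions are 12% and 17%. Neither fits a population made up only of patients who began palliative care at least 274 days before death.
- Reading B therefore contradicts the protocol's own population and cannot be what was meant.

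**Effect on numbers under Reading A (illustration only).** The plan's 4640 is a required number. It does not follow from the stated inputs under the usual formula: 12% against 17% needs 1556 patients in total at 80% power, the design effect with 263 per centre is 1 + 262 × 0.015 = 4.93, and 1556 × 4.93 ≈ 7671. The document states neither alpha nor power, so this uses assumed values; it is a separate matter. Two assumptions about the 12-month yield show how far the illustration depends on it. Power is for the two-proportion test with n per arm divided by the design effect.

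| Assumed yield of the full window | Per centre | Design effect | Power | After losing 25% | Per centre | Design effect | Power |
|---|---|---|---|---|---|---|---|
| 4640 | 154.7 | 3.305 | 76% | 3480 | 116 | 2.725 | 72% |
| 30 × 263 = 7890 | 263 | 4.93 | 81% | about 5918 | 197.25 | 3.944 | 79% |

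In the first row, n per arm after the design effect is 2320/3.305 ≈ 702 before and 1740/2.725 ≈ 639 after. The power loss is about 4 percentage points in the first row and about 3 in the second. In the second row the reduced yield is still above 4640.

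**The case against.** Four points can be made against the concern.

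- **The two sentences may be compatible.** One gives a review date, the other a death window, and they name different origins. An origin at least 3 months before study onset, such as a programme start, would let a review at month 18 reach month 21 of the window. The study-design figure is not available here and may show a timeline. This stands as a possibility, but the text states no such origin, so a reader would have to supply it.
- **The patient-level reading is a slip of wording.** This stands. The cause-of-death denominator in three sections and the 12% control rate show that unidentified patients belong in the analysis. A window that opens 9 months after a centre-level start would also make sense, since every death in it leaves more than 90 days in which early identification could have happened.
- **A reader might infer that the primary outcome will be about 100% in both arms, so that no effect can be estimated.** The documents do not support this as a planned consequence, for the reason just given. Even on the literal wording it goes too far: the outcome counts identification by GPs and nurses in the electronic record, and palliative care begun by a hospital unit or home team without that record would not count.
- **A reader might infer a firm loss from 4640 to 3480 records.** The protocol gives 4640 as the number needed, not as the yield of twelve months of deaths. The arithmetic is right, but the premise is assumed.

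The two defects also rest on alternative readings and do not hold together. What remains is that each natural reading leaves the sentence wrong or incomplete.

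**Conclusion.** The point holds as a failure to fix the death window and its origin. It does not show that the planned analysis population is unusable.

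With a shared study-level origin, the review date precedes the end of the window by 3 months, and about 25% of the window's deaths would be missing if deaths are evenly spread. The power consequence is modest: from 76% to 72% if 4640 is the 12-month yield, and less under the alternative assumption. It is an illustration and not the main reason to act. With a patient-level origin, the wording excludes patients who never started palliative care and contradicts the protocol's denominator and control rate; it should be treated as an error of expression and replaced.

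The main reason to act is that this sentence settles the denominator of the primary outcome, and no other sentence in the article settles it. The documents do not show which of 18 and 21 months is the intended limit.

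**What to change.** State the same rule in Design and in Data collection:

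- One death window, counted from one common centre-level date (the start of the intervention), with the same calendar dates in intervention and control centres.
- Included: all adults registered at a randomised centre who died in that window of a listed cause, whether or not palliative care was ever started.
- Remove the present origin from the Data collection sentence.
- Reconcile the 18-month review with the end of the window, and extract records only after the window has closed. If month 21 is the end, the review moves to after month 21. If the review must stay at month 18, the window has to end by then and the expected number of deaths should be restated.

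The cost is a change of wording in two sections and, if the 9 to 21 month window is kept, a later extraction date. No new data items are needed.

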### Sample size

It is necessary to prospectively analyze 4640 clinical records of deceased patients from the defined population (causes of death: ICD codes C00-C97; 100–152, 160–169, N17, N18, N28, 112, 113, K70-K77, J06-J18, J20-J22, J40-J47, J96, G10, G20, G35; G122, G903, G231.F01, F03, G30, R54, B20-B24) to detect an increase of at least 5% in the proportion of patients identified as needing PC at 1 month before death in the intervention arm, assuming that 12% of patients will need PC in the control arm, a median of 263 patients in each health care center (cluster size), and an intra-class correlation coefficient of 0.015 [34].

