Initially, caregivers only proposed PC when active treatment could not be prolonged, although it is has long been established that PC must start when active treatment is on-going [13]. There is a general agreement that patients suitable for PC should be identified as soon as possible. The World Health Organization (WHO) emphasized early identification in its definition of PC since 2002: “an approach that improves the quality of life of patients and their families facing the problems associated with life-threatening illness, through the prevention and relief of suffering by means of *early identification* and impeccable assessment and treatment of pain and other problems, physical, psychosocial and spiritual” [14]. Subsequent studies reported that early PC can even prolong survival in patients with some tumors [15, 16]. Thus, the early identification of patients eligible for PC has many benefits, in that aggressive diagnostic and therapeutic interventions are avoided, and unnecessary suffering and costs are reduced [17, 18].

It is important to determine how often PC is needed and the service requirements to calculate the necessary resources. Up to 75% of patient deaths in Spain are due to chronic illnesses from advanced identifiable processes [7]. Murtagh et al. [10] estimated that 63% of deaths were eligible for PC. It is also necessary to determine the incidences of advanced stages of the different pathologies, and this can be estimated from mortality rates. It is also essential to establish the suitable timing for administration of PC [19]. This timing is difficult to predict [20], but an approximation will allow calculation of the prevalence of the problem, planning of services, and estimation of program coverage [21].

The prevalence of cases needing PC will increase with the incidence of the chronic illnesses, the number of eligible pathologies, and the development of PC services. Thus, the need for PC will continue to grow over time. It is therefore essential to identify patients who can only be cared for by conventional services in a primary care or hospital setting, and patients who need specific PC resources (home- or hospital-based), exclusively or in combination with conventional services. The sustainability of the PC model must be based on a shared care model, in which there are general or conventional care services and specialized PC resources [22].

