### Setting

IB Salut is a public health organization in the Spanish National Health System, in which universal tax-funded health care services are provided to every citizen, and services are free at the point of access. Each patient is registered with one primary health care center. The Balearic Health Care Service covers the entire population of the Balearic Islands. Majorca is the largest island (850,000 inhabitants), and has four health districts (North, South, East and West Health Districts), each of which has a general hospital and several primary health care centers. PC services in Mallorca Island are provided by 3 PC units in non-acute hospitals and a PC home-based service, with 7 teams of physicians, nurses, and psychologists.

Primary health care centers from 3 health districts in Majorca will participate in the study. The intervention will be managed in the North Health District, which has 6 primary health care centers.

The intervention will be evaluated in 2 health districts: the South Health District (264,757 inhabitants), which has a university hospital and 14 primary health care centers, and the East Health District (326,988 inhabitants), which has a general hospital and 16 primary health care centers.

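### The assumed median of 263 eligible deaths per centre disagrees with 4640 over 30 centres and is not credible for the stated catchment and 12-month window; whether 4640 is reachable is left open

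*Protocol article*

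**What the plan says.** All references are to the protocol article.

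- **Sample size:** "It is necessary to prospectively analyze 4640 clinical records of deceased patients from the defined population". The inputs are 12% in the control arm, an increase of at least 5% (read here as 12% versus 17%), an intra-class correlation of 0.015 and "a median of 263 patients in each health care center (cluster size"). The abstract repeats the total: "Sample size: A total of 4640 deceased patients". No significance level or power is given.
- **Randomization:** 30 centres, in blocks of six, read here as 15 per arm.
- **Setting:** evaluation takes place in two of the island's districts. One of them is "the South Health District (264,757 inhabitants), which has a university hospital and 14 primary health care centers". The other one is described as "the East Health District (326,988 inhabitants), which has a general hospital and 16 primary health care centers".
- **Data collection:** the records are those of "patients who died 9 to 21 months after the onset of PC" from a listed set of causes. The **Design** section places the record review at 18 months after study onset.
- **Background:** one cited study "estimated that 63% of deaths were eligible for PC", and "Up to 75% of patient deaths in Spain are due to chronic illnesses from advanced identifiable processes". No death rate for the two districts is given.

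**The concern.** The analysed units are deaths from listed causes in a defined population over a defined period. Their number is population x death rate x eligible share x time, and recruitment effort cannot raise it. A planned cluster size can therefore be checked against the catchment.

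The cluster size matters because it sets the design effect, and through it the required number and the power. If 263 is wrong, the calculation built on it is wrong. If the supply of deaths also falls short of 4640, the trial will be less precise than its stated size suggests, and a null result may be read against a difference that it could not reliably detect.

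**Working it through.** **1. The plan's own figure.** With p1 = 0.12, p2 = 0.17, two-sided 5% and 80% power (both assumed, since neither is stated), the individually randomised size is 778 per arm. The design effect at m = 263 is 1 + 262 x 0.015 = 4.93, so N = 2 x 778 x 4.93 = 7,671. One-sided 5% gives 2 x 613 x 4.93 = 6,044. No combination tried with m = 263 (one- or two-sided 5%; 80%, 85% or 90% power; with or without continuity correction) gives 4640. The nearest result uses m = 154.7, one-sided 5% and 85% power (4,706), which is not the stated cluster size.

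**2. The total against the cluster size.**
- 4640/30 = 155 per centre.
- 30 x 263 = 7,890.
- 4640/263 = 17.6 centres.
- Taken strictly as a median, 263 means at least 15 centres with 263 or more, so at least 15 x 263 = 3,945 deaths. At most 4640 - 3,945 = 695 remain for the other 15, about 46 each.

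**3. The cluster size against the catchment.** 264,757 + 326,988 = 591,745 people, or 19,725 per centre, which agrees with the mean of 20,000 registered patients given in the Background. If 263 is typical:
- eligible deaths needed: 7,890/591,745 = 13.3 per 1000 in 12 months;
- all-cause rate needed: 13.3/0.75 = 17.8 to 13.3/0.63 = 21.2 per 1000.

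About 2% of all inhabitants would have to die in the year. If every death were eligible, the rate would still have to be 13.3 per 1000.

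**4. The total against the catchment.** 4640/591,745 = 7.84 eligible deaths per 1000.

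| Window | Eligible share | All-cause rate needed per 1000 per year |
|---|---|---|
| 12 months | 63% | 12.4 |
| 12 months | 75% | 10.5 |
| 12 months | 85% (assumed) | 9.2 |
| 18 months (if so used) | 63% | 8.3 |
| 18 months (if so used) | 75% | 7.0 |

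**5. Yield and power at an assumed death rate.** The rates are assumptions, not figures from the article. Yield = 591,745 x rate x share over 12 months. With m = N/30, n_eff = 15m/[1 + (m - 1) x 0.015] per arm and power = Phi(0.05/sqrt[(0.12 x 0.88 + 0.17 x 0.83)/n_eff] - 1.96).

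| All-cause rate per 1000 | Eligible deaths (63% to 75%) | Per centre | Power |
|---|---|---|---|
| 6 | 2,237 to 2,663 | 75 to 89 | 64% to 67% |
| 7 | 2,610 to 3,107 | 87 to 104 | 67% to 70% |
| 8 | 2,982 to 3,550 | 99 to 118 | 70% to 72% |
| 9 | 3,355 to 3,994 | 112 to 133 | 71% to 74% |
| 10 | 3,728 to 4,438 | 124 to 148 | 73% to 75% |
| 11 | 4,101 to 4,882 | 137 to 163 | 74% to 77% |
| 12 | 4,474 to 5,326 | 149 to 178 | 75% to 78% |

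For comparison, 4640 over 30 centres has m = 154.7, design effect 3.305, n_eff = 702 per arm and power 76%. At 263 in every centre, n_eff = 800 and power is 81%. The difference detectable with 80% power is 5.3 points at 4640 and about 5.7 points at 3,000.

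**The case against.** A reader might infer that the trial cannot reach 4640 and so overstates what it will analyse. The documents do not support that, for three reasons.

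- **Death rate.** None is given. A range that stops at 10 per 1000 ends just below the 10.5 at which 4640 is met with 75% eligible. Extended to 12 per 1000, the yield straddles 4640.
- **Eligible share.** The 63% and 75% come from general statements in the Background and are not tied to the broad cause-of-death list that defines the analysed population. At 10 per 1000, a share of 7.84/10 = 78.4% would be enough.
- **Window.** Data collection and Design are not reconciled, and the time origin in Data collection is unclear. A full 18 months of deaths would make 4640 easier to reach. However, Design gives only the time of the review and does not describe 18 months of accrual. If both clocks start together, a review at month 18 would capture only 9 months of deaths, and 4640 would need 13.9 to 16.6 per 1000.

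These objections stand against the 4640 shortfall. They do not rescue 263: the conflict with 155 needs no death rate, and even 18 months of deaths would require 11.9 to 14.1 per 1000.

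Two further objections also carry weight. The power loss is modest, because the number of centres and the intra-class correlation limit precision more than the number of deaths does. And since no power is stated, there is no declared target to miss. A journal article may also leave death counts to the full protocol, so their absence is not itself the defect.

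**Conclusion.** The point holds for the cluster size. A median of 263 sits badly with 4640 deaths in 30 centres and, if typical, implies 17.8 to 21.2 deaths per 1000 from all causes at the cited shares. The design effect of 4.93 that follows from it should not be relied on. Strictly, a median of 263 within a total of 4640 is possible, but only with a split between large and small centres that the article does not describe.

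For 4640 itself, the conclusion is conditional on death rate, eligible share and window. Over 12 months at an assumed 6 to 10 per 1000 and 63% to 75% eligible, there would be a shortfall, and power would be about 1 to 12 points below the 76% at 4640. These power figures assume 12% versus 17%, intra-class correlation 0.015, 15 equal centres per arm, two-sided 5% and the normal approximation.

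The sample size text should be corrected, but the expected effect on power is moderate.

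**What to change.** 1. Reconcile the death window in Data collection with the 18-month review in Design, and state the time origin.
2. Replace the median of 263 with the expected eligible deaths per centre, taken from the health service's own listed-cause death counts for the 30 centres in the last year before the trial.
3. Recompute the design effect at that size. Show the required number, the expected number, the power and the detectable difference side by side for 30 centres, with the significance level and target power. Keep the required number visible beside the forecast. For illustration, 3,000 deaths (100 per centre) would give about 70% power for 12% versus 17%.
4. State that all eligible deaths in the window are analysed.

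The cost is one tabulation of past deaths and a rewritten paragraph. The stated size may look less favourable. No extra enrolment is needed.

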### Randomization

Each of the 30 participating primary health care centers will be randomly assigned to the intervention or control group. Randomization and concealment will be centralized, through a single coordinating center, using a computer-generated block randomization in blocks of six.

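### The sample size is stated for identification at 1 month before death, while the primary outcome is identification 90 days before death, so it is unclear whether the 12% and the 5% increase apply to the primary outcome

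*Protocol article*

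**What the plan says.** The Primary outcomes section of the protocol article defines the outcome as "Early identification (90 days before death), by GPs and nurses, of patients who are least 18 years-old and need PC", taken from electronic records. The measurements paragraph of the abstract gives the same window with an inequality sign: "Early identification (>90 days before death".

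The Sample size section requires 4640 records of deceased patients "to detect an increase of at least 5% in the proportion of patients identified as needing PC". It completes that phrase with a different time point: "in the proportion of patients identified as needing PC at 1 month before death in the intervention arm". The control value is introduced as "assuming that 12% of patients will need PC in the control arm". The clustering inputs are "a median of 263 patients in each health care center (cluster size") and "an intra-class correlation coefficient of 0.015". Neither alpha nor power is stated there.

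The Secondary outcomes section contains no identification outcome at 1 month. Its final-month items are admissions, emergency visits, indicators of aggressive care, and cost. No section reconciles the 1-month and 90-day windows.

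**The concern.** A sample size should rest on the control proportion and target difference of the primary outcome. Here the only sample-size statement names an event that is not among the trial's listed outcomes.

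The two events are nested. A patient identified at least 90 days before death has also been identified by 1 month before death. The 90-day proportion therefore cannot exceed the 1-month proportion and will normally be lower. If 12% was obtained for the 1-month event, it is only a ceiling for the control rate of the primary outcome.

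The wording of the 12% adds to the doubt. The denominator is already restricted to deaths from causes chosen as potentially needing palliative care, so a 12% share who need it makes little sense. A share identified does make sense, but the text does not say so and attaches no time window to the figure.

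At stake is whether 4640 records say anything about the trial's ability to answer its primary question.

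**Working it through.** **Inputs from the protocol.** Total 4640 records; 30 centres (Randomization: "Each of the 30 participating primary health care centers will be randomly assigned to the intervention or control group"); control 12%; increase 5%; ICC 0.015; cluster size 263.

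**Assumptions.** Two-sided alpha 0.05; equal arms of 4640/2 = 2320; 5% read as percentage points, so 12% against 17%. (A relative 5% increase, 12% to 12.6%, would need about 94,000 patients even without clustering, at 80% power.)

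**Design effect**, DE = 1 + (m − 1) × ICC:
- Stated cluster size, m = 263: 1 + 262 × 0.015 = 4.93.
- Cluster size implied by the total, m = 4640/30 = 154.7: 1 + 153.67 × 0.015 = 3.305.

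**The plan's own figure.** For 12% against 17% at an assumed 80% power, the unclustered size is 778 per arm. This gives 2 × 778 × 4.93 = 7671 records with m = 263, or 2 × 778 × 3.305 = 5143 with m = 154.7. Neither is 4640. That gap concerns cluster size and total (30 × 263 = 7890), not the time window, so both design effects are carried below and only changes from the 12% row bear on this point.

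**Power at 4640.** Power = Φ(|p1 − p0|/SE − 1.96), with SE = √(DE × [p0(1 − p0) + p1(1 − p1)]/2320).

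Examples with DE 3.305:
- p0 = 0.12, p1 = 0.17: SE = √(3.305 × (0.1056 + 0.1411)/2320) = 0.01875; 0.05/0.01875 = 2.667; power Φ(0.707) = 76%.
- p0 = 0.06, ratio 17/12 kept, p1 = 0.085: SE = 0.01383; 0.025/0.01383 = 1.808; power Φ(−0.152) = 44%.
- p0 = 0.06, 5 points kept, p1 = 0.11: SE = 0.01483; 0.05/0.01483 = 3.372; power Φ(1.412) = 92%.

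The protocol gives no 90-day control rate, so a range is shown:

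| Assumed 90-day control rate | Ratio 17/12 kept, DE 3.305 | 5 points kept, DE 3.305 | Ratio 17/12 kept, DE 4.93 | 5 points kept, DE 4.93 |
|---|---|---|---|---|
| 12% | 76% | 76% | 59% | 59% |
| 10% | 67% | 81% | 50% | 64% |
| 8% | 56% | 87% | 41% | 71% |
| 6% | 44% | 92% | 32% | 79% |
| 4% | 31% | 97% | 22% | 88% |

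A lower control rate reduces power on the ratio scale and raises it on the difference scale. Keeping 5 points from a 6% base means a relative risk of 11/6 = 1.83, against 17/12 = 1.42 at the planned rates.

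**The case against.** The best reply is that the 1-month phrase is a slip. The 12% carries no window of its own, the final-month outcomes stand close by in the text, and both places that define the primary outcome say 90 days. If so, 12% and 17% may already be 90-day rates, and one phrase needs correcting. This is possible, but nothing in the protocol confirms it, so the authors still have to say which window the figures describe.

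Three stronger readings are tempting and are not supported:

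- *The trial is underpowered because of the mismatch.* The planned effect is worded as an increase in a proportion. Read as 5 points, a lower control rate raises power. The ratio matters too, because the Statistical analysis section estimates a relative risk, but the protocol does not fix the effect on that scale. There is also no stated power that could fall: any power figure is implied by 4640 records and an assumed alpha. Values below 80% in the 12% row come from cluster size and total.
- *The protocol has two rival primary outcomes, open to choice after the data are seen.* Where the outcome is defined, it is consistently 90 days. A sample-size sentence does not define an endpoint, and identification at 1 month appears in no outcome list.
- *This is an arithmetic error.* The time-window conflict is between two statements; no calculation is shown to be wrong by it.

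**Conclusion.** The inconsistency stands. The Sample size section names a 1-month event, the primary outcome is a 90-day event, and the 12% is worded as need and not as identification. As written, the 12% and the 5% increase cannot be tied to the primary outcome, and the only sample-size basis names an event that the trial does not list as an outcome.

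The size of the consequence is conditional on 12% being a 1-month rate. In that case, halving the control rate to 6% moves the implied power by roughly 30 points down or 15 to 20 points up, depending on effect scale and cluster size. The 6% is illustrative, as no 90-day rate is given. These figures also rest on two-sided alpha 0.05, equal arms, equal cluster sizes and ICC 0.015. If the 1-month phrase is a slip, the window has no effect on power and the defect is one of wording.

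**What to change.** In the Sample size section:

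1. Replace the 1-month time point with the 90-day window of the Primary outcomes section and the abstract, worded identically in all three places.
2. State the control and target proportions for that window. Either confirm that 12% and 17% are 90-day rates, or replace them, for example with the proportion found in eligible deaths before the intervention in the same electronic record.
3. Say that the 5% is in percentage points, if that is meant, and restate the power or detectable difference of 4640 records on this basis, with alpha and sidedness.
4. Describe the 12% as patients who will be identified as needing palliative care.

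The cost is a wording change and at most one recalculation. The implied power may move in either direction. Trial conduct and data extraction do not change.
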